## Abstract

**Background:**

Embolization of atherosclerotic debris from the rupture of a vulnerable atherosclerotic plaque occurs iatrogenically during percutaneous coronary interventions (PCI) and can induce myocardial necrosis. These microembolizations are detected as high intensity transient signals (HITS) using intracoronary Doppler technology.

**Presentation of the hypothesis:**

In the presented study we will test if abciximab (ReoPro®) infusion reduces high intensity transient signals in patients with stable angina pectoris undergoing PCI in comparison to standard therapy alone.

**Testing the hypothesis:**

The High Intensity Transient Signals ReoPro® (HITS-RP) study will enroll 60 patients. It is a prospective, single center, randomized, double-blinded, controlled trial. The study is designed to compare the efficacy of intravenous abciximab administration for reduction of microembolization during elective PCI. Patients will be randomized in a 1:1 fashion to abciximab or placebo infusion. The primary end point of the HITS-RP-Study is the number of HITS during PCI measured by intracoronary Doppler wire. Secondary endpoints are bleeding complications, elevation of cardiac biomarkers or ECG changes after percutaneous coronary interventions, changes in coronary flow velocity reserve, hs-CRP elevation, any major adverse cardio-vascular event during one month follow-up.

**Implications of the hypothesis:**

The HITS-RP-Study addresses important questions regarding the efficacy of intravenous abciximab administration in reducing microembolization and periprocedural complications in stable angina pectoris patients undergoing PCI.

**Trial registration:**

The trial is registered under http://www.drks-neu.uniklinik-freiburg.de/drks_web/:DRKS00000603.

## Background

Following percutaneous coronary intervention (PCI) an increase of cardiac marker enzymes is relatively often observed and associated with reduced coronary flow velocity reserve (CFVR) [1]. Serum concentration of cardiac troponin I (cTNI) was reported to be increased in 30–40% of cases [2]. The troponin rise is the result of myocardial necrosis during PCI induced by embolization of atherosclerotic and thrombotic debris during balloon or stent inflation [3]. Troponin elevation is associated with dismal prognosis in patients with unstable angina [4] and PCI [5]. Periprocedural coronary microembolization occurs in about 25% of all PCIs. The incidence ranges from 0 to 70%, depending on the method of assessment [6]. Coronary microembolization is a common event during several phases during PCI. Even passing of the stenosis with the stent or balloon may be a vulnerable phase [7].

The consequences of coronary microembolization are microinfarctions with an inflammatory response, contractile dysfunction, perfusion-contraction mismatch, and reduced CFVR [8]. The number of microparticles correlate to the size of myocardium at risk in patients with ST-elevation myocardial infarction [9].

The intracoronary Doppler guidewire is a feasible device for detection and quantification of microembolism occurring during PCI [10]. In a previous study we could demonstrate that the incidence of procedural associated non-ST elevation myocardial infarction (pNSTEMI) is correlated to the frequency of Doppler-detected microemboli [7].

Several clinical studies unravelled that cardiac biomarker elevations directly correlated with the extent of myocardial necrosis [11]. In patients with pNSTEMI the myocardial damage represents up to 5% of the left ventricular mass [12].

The progressive contractile dysfunction results from an inflammatory reaction to microinfarctions. Elevation of high-sensitivity C-reactive protein (hs-CRP) levels providing prognostic information for patients receiving PCI [13] and could be derived directly from inflammation or from secondary reaction to microinfarctions due to microembolization [14]. This inflammation marker could be used as a predictor for early complications after stent deployment [15].

### Presentation of the hypothesis

The mouse monoclonal antibody abciximab against the platelet receptor glycoprotein IIb/IIIa (GPIIb/IIIa) is able to inhibit platelet aggregation by more than 80% [16]. In patients with acute myocardial infarction abciximab was able to improve myocardial microcirculation and reduce infarct size due to dissolution of thrombi and microemboli [17]. Therefore we hypothesize that abciximab is a possible agent to reduce coronary microembolization in patients with stable CAD undergoing elective PCI.

### Testing the hypothesis

The HITS-RP study is a prospective, double-blinded, randomized, placebo controlled trial in patients with coronary artery disease (CAD) undergoing PCI. The study goal is to determine the efficacy of intravenous abciximab bolus application with subsequent 12-hour intravenous infusion in reducing high intensity transient signals (HITS) compared to placebo. The trial is registered under http://www.drks-neu.uniklinik-freiburg.de/drks_web/:DRKS00000603.

### Primary and secondary outcome

The primary study end point of the HITS-RP study is the incidence of HITS during PCI. Secondary endpoints are changes in CFVR, cardiac biomarkers (cTNI, CK, CK-MB) and hs-CRP in comparison to the initial values, ECG changes, bleeding complications due to the additional thrombocyte inhibiton, and any type of major adverse cardiac or vascular event during one month follow-up. Bleeding complications will be assessed according to the GUSTO criteria (a-severe or life-threatening; b-moderate; c-mild) [18].

### Patient population

The prospective study will include 60 consecutive patients with CAD and elective PCI. Recruitment will commence in may 2012. The Institutional Ethics Committee of University Hospital of Jena approved the study protocol.

#### Inclusion criteria

Patients are eligible for the study if they are between 18 and 80 years of age. Inclusion criteria are stable angina pectoris and written informed consent.

#### Exclusion criteria

The exclusion criteria were (1) increase of cardiac markers before PCI, (2) left bundle-branch block, (3) terminal renal insufficiency, (4) hypothyroidism, (5) skeletal muscle injury, (6) chronic occluded target artery, (7) bifurcation lesion, (8) in-stent restenosis, (9) planned multivessel intervention, (10) side branch occlusion or (11) prolonged vasospasm and (12) any contraindication for antiplatelet medication.

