### Patient treatment

All patients receive 100 mg acetylsalicylic acid once daily before PCI and thereafter according to the standards of good clinical practice. Those patients not already taking clopidogrel medication will receive 600 mg immediately after PCI and afterwards 75 mg once daily. A heparin bolus of 70 IU Heparin/kg body weight is given following the insertion of the arterial sheath. All other medication is given at the discretion of the attending cardiologist. After diagnostic angiography with knowledge of the coronary anatomy patients are planned to undergo balloon dilatation with implantation of a stent for a single stenosis. The choice of stent (bare-metal or drug-eluting stent) is left to the discretion of the attending cardiologist. Patients will be randomly assigned to the glycoprotein IIb/IIIa receptor antagonist abciximab or placebo. The study drug will be given as an i.v. bolus of 0.25 mg/kg body weight 10 minutes before PCI followed by a continuous infusion at 0.125 μg/kg/min initiated immediately after the bolus and continued for 12 h. A Doppler guidewire is positioned 1 to 2 cm distal to the stenosis for PCI. At this position the average peak velocity (APV) is recorded. Before and after each interventional step CFVR is measured as the ratio of maximum APV and baseline APV. Maximum hyperemia will be induced by intracoronary injection of 30–40 μg adenosine. The number of HITS will be measured as previously described [7].

After PCI, removal of the sheath is performed according to local practice. Care must be taken to ensure adequate hemostasis.

After 12 and 24 h creatine kinase (CK), creatine kinase-MB (CK-MB), cardiac troponin I (cTNI), hemoglobin (Hb), hs-CRP will be determined and after 24 h also an ECG will be recorded. At 30-day follow-up all cause mortality, myocardial infarction, angina pectoris, new congestive heart failure, and bleeding complications will be assessed. This is the end of the trial.

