### Data and statistical analysis

The primary end point will be analyzed according to the intention-to-treat principle using the independent-samples t-test. In addition per-protocol analysis and to adjust for risk factors (such as diabetes, hypertension, smoking, cholesterol level, sex) multivariate regression analysis will be performed. The secondary endpoints are compared using Student’s t-test, Mann–Whitney U test, chi-square test and Fisher’s exact test as appropiate and by multivariate regression models.

All data will be collected independently in a blinded database by an external data management facility (2conduct clinical trials). A p-value of <0.05 will be considered as statistically significant. Data analysis will be performed using SAS 9.3 (SAS Institute Inc.).

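### Side branch occlusion and prolonged vasospasm are exclusions with no time limit; read as events of the PCI, they conflict with the intention-to-treat primary analysis and could bias it in either direction

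*Protocol article*

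**What the plan says.** The protocol article, Exclusion criteria, lists twelve items. Two of them, "10) side branch occlusion or (11) prolonged vasospasm", carry no timing. Others on the list do, or describe what can be known beforehand: the first is "1) increase of cardiac markers before PCI", the ninth concerns multivessel work that is planned, and lesion anatomy has its own entries, "6) chronic occluded target artery, (7) bifurcation lesion, (8) in-stent restenosis".

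Patient treatment describes diagnostic angiography, then random assignment, and fixes the dosing time: "The study drug will be given as an i.v. bolus of 0.25 mg/kg body weight 10 minutes before PCI".

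Under Primary and secondary outcome, "The primary study end point of the HITS-RP study is the incidence of HITS during PCI".

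Data and statistical analysis states: "The primary end point will be analyzed according to the intention-to-treat principle using the independent-samples t-test". A per-protocol analysis is planned as an addition.

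No section says whether a randomised, dosed patient who then meets criterion (10) or (11) is kept, dropped or replaced.

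**The concern.** An exclusion criterion is safe for a randomised comparison when it can be checked before allocation. Side branch occlusion and prolonged vasospasm are ordinarily complications of wiring, ballooning or stenting. On that reading they become known only after the patient has been allocated and dosed.

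A site that applies the list literally would then drop treated patients because of something that happened after randomisation. Two features make this more than untidy. The study drug is already running, so the chance of the event may differ by arm. And the event arises in the same procedure in which the primary endpoint is counted, so it may be related to the HITS count. If both hold, the groups compared are no longer those that were randomised. Blinding does not prevent this: if the drug changes the event rate, blinded removal is still unequal. Biomarkers, ECG and CFVR, all secondary endpoints, would be exposed in the same way.

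**Working it through.** **1. Order of events.** Dosing requires allocation, and the bolus precedes the PCI by 10 minutes (Patient treatment). Whatever the exact moment of randomisation, anything that arises during the PCI therefore comes after both.

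**2. Do criteria (10) and (11) mean events of the PCI?** The article does not say. The list points that way: criterion (1) is tied to the time before PCI, (9) to what is planned, and (6) to (8) already cover lesion anatomy. Only (10) and (11) name typical procedural complications, and they have no such limit. This is an inference.

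**3. The two statements side by side.** On the procedural reading, a dosed patient with a side branch occlusion is excluded under Exclusion criteria and retained under the intention-to-treat sentence. The article does not say which prevails.

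**4. The plan's own sample size.** Inputs from Power calculation: means 27 and 18 (difference 9), SD 12, two-sided alpha 0.05, power 80%. Noncentral-t power with n per arm uses df = 2n − 2 and noncentrality 9 / (12 × √(2/n)).

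| n per arm | Power |
|---|---|
| 27 | 77.2% |
| 28 | 78.7% |
| 29 | 80.1% |
| 30 | 81.5% |

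The stated 29 per group is reproduced. The drop-out allowance is 30 − 29 = 1 patient per arm, or 2 in all. Losing 3 or more of 60 puts at least one arm below 29.

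**5. How easily is the allowance used up?** The event rate is not in the article, so a range is assumed. The binomial probability of 3 or more events in 60 patients is 12% at a rate of 2%, 58% at 5% and 95% at 10%.

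**6. Bias.** Let p be the share removed in an arm and D the excess of the mean HITS count in removed over kept patients. The mean of those kept is the overall mean − p × D. Both p and D are assumed.

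| D | 10% placebo, 5% abciximab removed | 5% placebo, 10% abciximab removed |
|---|---|---|
| 6 | (27 − 0.6) − (18 − 0.3) = 8.7 | (27 − 0.3) − (18 − 0.6) = 9.3 |
| 12 | (27 − 1.2) − (18 − 0.6) = 8.4 | (27 − 0.6) − (18 − 1.2) = 9.6 |
| 24 | (27 − 2.4) − (18 − 1.2) = 7.8 | (27 − 1.2) − (18 − 2.4) = 10.2 |

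Equal rates with equal D leave the difference at 9. A negative D reverses the direction in each column.

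**7. Limit of the power table.** It holds SD at 12, so it describes only losses unrelated to HITS. If removed patients differ from the rest by D, the variance among those kept is 144 − p(1 − p)D². With p = 10% in each arm and D = 15, this is 144 − 0.09 × 225 = 123.75, SD 11.1, and power with 27 per arm is about 83%. Selective removal therefore need not lower power; its harm is bias.

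**The case against.** The strongest reply has three parts.

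First, the timing is inferred. A side branch already occluded, or spasm seen on the diagnostic angiogram, could be screened out before randomisation. The article never states the moment of randomisation, and the flowchart that might show it is not available. This stands as a limit on certainty. It does not remove the problem, because the wording permits the procedural reading and that reading is the more natural one.

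Second, no sentence removes anyone from the primary analysis. A patient who meets (10) or (11) after dosing could stay in the intention-to-treat set and leave only the per-protocol set, and definitions of analysis sets are commonly left to a fuller document. This also stands in part: a reader might infer that the article orders such patients to be dropped from the primary comparison, and it does not. But an exclusion criterion that cannot be checked before dosing is a stated rule, not a missing detail, and the text gives a site no reason to keep the data.

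Third, a reader might infer that removed patients would be those with many HITS, more often in the placebo arm, so that the effect is diluted. Nothing in the article links either event to HITS counts. Its Discussion names multivessel disease, more than 20 microemboli and high inflation pressure as risks for procedural infarction, and neither of these two events. The event rate may also be low, since bifurcation lesions, chronic occlusions and planned multivessel work are already excluded. Neither the direction nor the size of a bias can be asserted.

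**Conclusion.** The point holds as a defect in how the two criteria are fixed. On the natural reading they are post-dosing events, and excluding on them is incompatible with the intention-to-treat primary analysis. It does not show that patients will be dropped, nor that the result will be biased in a known direction.

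The size is open. If losses are equal and unrelated to HITS, the cost is about 3 percentage points of power at 28 per arm and 4 at 27, against 30 per arm. If removal is unequal and related to HITS, the 9-HITS difference moves by at most 1.2 in either direction over the scenarios shown, which rest on assumed rates of 5% and 10% and an assumed gap of up to 24 HITS. The correction is worth making before recruitment: if data on dropped patients are not collected, the randomised comparison cannot be restored.

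**What to change.** - Delete criteria (10) and (11), or limit them to findings present on the diagnostic angiogram before randomisation.
- State that every randomised patient with a Doppler recording stays in the primary intention-to-treat analysis with the HITS counted, whatever happens during the PCI.
- Leave out patients with side branch occlusion or prolonged vasospasm only in the per-protocol analysis already planned, or in a labelled sensitivity analysis.

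The cost is a few sentences and no extra patients; the sample size stays at 30 per arm. The one downside is slightly more variable HITS values from complicated procedures.

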### Randomization

Patient randomization is performed centrally with a randomization ratio of 1:1 (n = 30 patients per group). Patients will be randomized by blockwise randomization with a fixed block size of 6 using Datinf randList 1.2. The random number generator is based on the algorithm of Park and Miller with Bays-Durham correction. Allocation concealment is done in the pharmacy. Medication will be delivered in black syringes with a label only containing study name and patients number (Figure 1).

**Figure 1 F1:**
[figure not shown]
ReoPro HITS flowchart.

### Power calculation

Based on the results of previous studies [7] we expect 27 HITS on average in the placebo group and 18 HITS in the treatment group. Assuming a standard deviation of 12 in both groups, we will need a sample size of 29 patients to detect the treatment effect with a power of 80% at a two-sided alpha-level of 0.05. To account for drop-outs we have chosen to include 30 patients per group in the study.

### Patient treatment

All patients receive 100 mg acetylsalicylic acid once daily before PCI and thereafter according to the standards of good clinical practice. Those patients not already taking clopidogrel medication will receive 600 mg immediately after PCI and afterwards 75 mg once daily. A heparin bolus of 70 IU Heparin/kg body weight is given following the insertion of the arterial sheath. All other medication is given at the discretion of the attending cardiologist. After diagnostic angiography with knowledge of the coronary anatomy patients are planned to undergo balloon dilatation with implantation of a stent for a single stenosis. The choice of stent (bare-metal or drug-eluting stent) is left to the discretion of the attending cardiologist. Patients will be randomly assigned to the glycoprotein IIb/IIIa receptor antagonist abciximab or placebo. The study drug will be given as an i.v. bolus of 0.25 mg/kg body weight 10 minutes before PCI followed by a continuous infusion at 0.125 μg/kg/min initiated immediately after the bolus and continued for 12 h. A Doppler guidewire is positioned 1 to 2 cm distal to the stenosis for PCI. At this position the average peak velocity (APV) is recorded. Before and after each interventional step CFVR is measured as the ratio of maximum APV and baseline APV. Maximum hyperemia will be induced by intracoronary injection of 30–40 μg adenosine. The number of HITS will be measured as previously described [7].

After PCI, removal of the sheath is performed according to local practice. Care must be taken to ensure adequate hemostasis.

After 12 and 24 h creatine kinase (CK), creatine kinase-MB (CK-MB), cardiac troponin I (cTNI), hemoglobin (Hb), hs-CRP will be determined and after 24 h also an ECG will be recorded. At 30-day follow-up all cause mortality, myocardial infarction, angina pectoris, new congestive heart failure, and bleeding complications will be assessed. This is the end of the trial.

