## Discussion

Coronary microembolization is a frequent event in ischemic heart disease, occurring artificially during coronary interventions. Especially patients with multivessel coronary artery disease, more than 20 microemboli, and high inflation pressure during PCI are at risk for pNSTEMI [7]. Thus, the protocol of the HITS-RP study is focused on patients undergoing elective PCI for stable CAD.

It is important to note that data for the use of filter devices during PCI were disappointing and no significant protection against microembolization was achieved in previous studies [19]. In consequence novel treatment strategies of preventing patients from pNSTEMI are desired.

Numerous studies demonstrated the effect of anti-platelet agents in patients with stable angina pectoris or acute coronary syndrome for attenuation of myocardial damage and reduction of adverse events [20,21]. However, it is still unclear whether the respective agent is able to reduce the formation of coronary microemboli. The glycoprotein IIb/IIIa receptor antagonist tirofiban reversibly suppressed HITS in the cerebrovascular circulation [22]. Thus, this clinical study is designed to identify a target for drug therapy of coronary microembolization and its consequences. In previous clinical trials, the benefits of abciximab infusion were achieved at the risk of increased bleeding [16]. It is necessary to mention that also the safety of abciximab infusion when added to antiplatelet therapy with aspirin and clopidogrel is an important question of the HITS-RP study.

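### Clopidogrel exposure differs between patients while HITS are counted, but the primary t-test does not adjust for it: a small, nearly free gain in precision is left unused

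*Protocol article*

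**What the plan says.** All places are in the protocol article.

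- **Endpoint** (Abstract, Testing the hypothesis): "The primary end point of the HITS-RP-Study is the number of HITS during PCI measured by intracoronary Doppler wire". It is complete when the procedure ends.
- **Background therapy** (Patient treatment): all patients have aspirin before PCI. For clopidogrel: "Those patients not already taking clopidogrel medication will receive 600 mg immediately after PCI and afterwards 75 mg once daily". The exclusion criteria neither require nor rule out earlier clopidogrel use.
- **Allocation** (Randomization): "Patient randomization is performed centrally with a randomization ratio of 1:1 (n = 30 patients per group"), and "Patients will be randomized by blockwise randomization with a fixed block size of 6 using Datinf randList 1.2". No stratification factor is named.
- **Primary analysis** (Data and statistical analysis): "The primary end point will be analyzed according to the intention-to-treat principle using the independent-samples t-test".
- **Additional analysis** (same section): "to adjust for risk factors (such as diabetes, hypertension, smoking, cholesterol level, sex) multivariate regression analysis will be performed". Clopidogrel is not among the examples.
- **Planning figures** (Power calculation): "we expect 27 HITS on average in the placebo group and 18 HITS in the treatment group", with an SD of 12 in each arm and 29 patients needed for 80% power at two-sided 5%, raised to 30 per arm.

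**The concern.** The trial tests whether a platelet inhibitor lowers HITS. Its own treatment rules create two states of background platelet inhibition at the moment HITS are counted: aspirin plus clopidogrel, or aspirin alone. The state is known before study drug is given.

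If clopidogrel also lowers HITS, two things follow. Its contribution to the spread of HITS stays in the error term of the t-test. And with 30 patients per arm, a chance imbalance in clopidogrel use moves the estimated difference up or down. A sponsor who plans on platelet inhibition lowering the count has its own reason to expect the factor to be prognostic. What is at stake is precision, and how readily readers will accept the result if the arms turn out unbalanced.

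**Working it through.** **1. The plan's own figure.** Inputs from Power calculation: difference 27 − 18 = 9, SD 12, two-sided 5%. The standard error at 30 per arm is 12 × √(2/30) = 3.10, so the noncentrality is 9 / 3.10 = 2.90. The noncentral-t calculation gives 80.1% power at 29 per arm and 81.5% at 30. The stated 29, read as per group, is reproduced (the normal approximation gives 28).

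**2. Power with adjustment.** Two inputs are missing from the documents and are assumed: p, the share already on clopidogrel (20% to 50%), and d, the mean HITS difference between patients on and not on clopidogrel (0 to 9). The total SD within each arm is held at 12. The share of variance explained is R² = p(1 − p)d²/144, and the residual SD is 12 × √(1 − R²). The test has 57 instead of 58 degrees of freedom.

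| d (HITS) | R², p = 0.2 / 0.5 | Residual SD | Power at 30 per arm |
|---|---|---|---|
| 0 | 0 / 0 | 12.00 | 81.5% |
| 3 | 0.010 / 0.016 | 11.94 / 11.91 | 81.9% / 82.1% |
| 6 | 0.040 / 0.063 | 11.76 / 11.62 | 83.0% / 83.9% |
| 9 | 0.090 / 0.141 | 11.45 / 11.12 | 84.9% / 86.9% |

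Example, p = 0.5 and d = 6: R² = 0.25 × 36 / 144 = 0.0625, and 12 × √0.9375 = 11.62.

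This formula ignores the small cost of chance correlation between arm and covariate. In a simulation of unstratified allocation (10,000 trials per setting, p = 0.5), power without and with adjustment was 81.9% and 81.3% at d = 0, 81.0% and 80.5% at d = 3, 82.2% and 83.9% at d = 6, and 81.9% and 86.4% at d = 9. So adjustment costs about half a point if clopidogrel hardly matters, and gains about 2 to 4 points if it matters as much as 6 to 9 HITS.

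**3. Chance imbalance.** With independent binomial counts in two arms of 30, the probability that the arms differ by at least 6 patients (20 points) is 7% at p = 0.2, 12% at p = 0.3 and 16% at p = 0.5. Such an imbalance shifts the estimated difference by 0.2 × d: 1.2 HITS at d = 6 and 1.8 at d = 9, against a standard error of 3.1. If it goes against abciximab, the expected difference falls to 7.8 or 7.2, and the chance of significance in that trial falls from 81.5% to about 70% or 63%. An imbalance the other way raises it.

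**4. Adjustment or stratification.** Simulated power at p = 0.5 and d = 9:

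| | t-test | Adjusted model |
|---|---|---|
| Unstratified | 81.9% | 86.4% |
| Stratified, blocks of 6 | 83.0% | 86.7% |

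Nearly all the gain comes from the model. Without stratification the t-test keeps its type I error at about 5%. With stratification it becomes conservative: 3.4% at d = 9 and 4.3% at d = 6.

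**The case against.** The strongest reply is that nothing here is an error. Under 1:1 randomisation an unadjusted t-test is valid whatever the background therapy, and its error rate already allows for chance imbalance. The Discussion calls it unclear whether antiplatelet agents reduce coronary microemboli, so d could be zero and the gain nil. The covariates are given only as examples, and an article may leave strata and the final list to the full protocol. All of this stands, and it limits the point to efficiency. It does not remove it: the article does fix the primary test, and that test is unadjusted. An extra covariate in the additional regression would not change the primary result.

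Stronger readings are tempting but not supported:

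- **That the comparison is biased.** Clopidogrel status precedes study drug and is balanced in expectation.
- **That clopidogrel has been ruled out as a covariate.** An open list cannot show that.
- **That the Discussion contradicts Patient treatment**, because it says "the safety of abciximab infusion when added to antiplatelet therapy with aspirin and clopidogrel is an important question". That sentence concerns safety. Patients not yet on clopidogrel receive it right after PCI, within the 12-hour infusion and before most of the bleeding follow-up, so the two sections are consistent.
- **That multivessel disease belongs in the primary model too.** The Discussion ties it to procedural infarction, not to the HITS count.
- **That adjustment would explain 10% to 20% of the variance.** At p = 0.5, clopidogrel alone would need an effect of 12 × √(0.10/0.25) = 7.6 HITS or 12 × √(0.20/0.25) = 10.7 HITS. The second exceeds the 9 assumed for abciximab.

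**Conclusion.** The point holds as a missed gain in precision and robustness. Exposure to clopidogrel differs by design while the primary endpoint is counted, and the fixed primary test makes no use of it. The size is modest. There is no gain if clopidogrel does not affect HITS, 2 to 3 power points or less for an effect up to 6 HITS, and 3 to 5 points if its effect equals the 9 HITS planned for abciximab. Protection against a 20-point imbalance, itself a 7% to 16% event, is the other benefit.

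These figures rest on assumed values of p and d, a total SD of 12, and the same treatment effect in both clopidogrel groups. The planned t-test and the sample size of 29 per group are both sound as they stand.

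**What to change.** - Record clopidogrel use before PCI (yes/no). The treatment rules already require staff to know it.
- Prespecify the intention-to-treat primary analysis as a linear model of HITS on arm and this variable.
- Keep the independent-samples t-test as sensitivity analysis.
- Report the difference in HITS between arms by clopidogrel status descriptively, without a test, so that readers can see which patients the average effect describes.

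Stratifying the allocation list by clopidogrel status is optional. It adds almost nothing once the model is adjusted, it may leave incomplete blocks, and it would make the sensitivity t-test conservative, which should then be stated.

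The cost is one analysis sentence, one degree of freedom and, if clopidogrel proves unrelated to HITS, about half a point of power. No extra patients and no change to treatment are involved.
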